## Abstract

**Background:**

Urinary tract infections (UTIs) are among the most common infectious diseases and drivers of antibiotic use and in-hospital days. A reduction of antibiotic use potentially lowers the risk of antibiotic resistance. An early and adequate risk assessment combining medical, biopsychosocial and functional risk scores has the potential to optimize site-of-care decisions and thus allocation of limited health-care resources. The aim of this factorial design study is twofold: first, for Intervention A, it investigates antibiotic exposure of patients treated with a protocol based on the type of UTI, procalcitonin (PCT) and pyuria. Second, for Intervention B, it investigates the usefulness of the prognostic biomarker proadrenomedullin (ProADM) integrated into an interdisciplinary assessment bundle for site-of-care decisions.

**Methods and design:**

This randomized controlled open-label trial has a factorial design (2 × 2). Randomization of patients will be based on a pre-specified computer-generated randomization list and independent for the two interventions. Adults with UTI presenting to the emergency department (ED) will be screened and enrolled after providing informed consent.

For our first Intervention (A), we developed a protocol based on previous observational research to recommend initiation and duration of antibiotic use based on the clinical presentation of UTI, pyuria and PCT levels. For our second intervention (B), an algorithm was developed to support site-of care decisions based on the prognostic marker ProADM and distinct nursing factors on days 1 and 3. Both interventions will be compared with a control group conforming to the guidelines.

The primary endpoints for the two interventions will be: (A) overall exposure to antibiotics and (B) length of physician-led hospitalization within a follow-up of 30 days. Endpoints are assessed at discharge from hospital, and 30 and 90 days after admission. We plan to screen 300 patients and enroll 250 for an anticipated estimated loss of follow-up of 20%. This will provide adequate power for the two interventions.

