### Sample size

#### Intervention A

The first co-primary objective is to show that the duration of antibiotic therapy in the index hospitalization is 2 days shorter in the PCT group (8 days, standard deviation ±5) than in the control group (10 days, standard deviation ±5). These estimates are based on a historical control group in our hospital [31,36]. According to these estimations, 99 patients per arm would provide an 80% power at the 5% alpha level.

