#### Intervention B

Similarly, for LOS estimation in patients with UTI we used data from a previous study performed on site at the Cantonal Hospital of Aarau during 2011, which approximated 6 days (standard deviation ±4) [36]. Our working hypothesis is that index hospitalization is 1.5 days shorter in the ProADM group (4.5 days, standard deviation ±4). According to these estimations, 112 patients per arm would provide an 80% power at the 5% alpha level (total sample size 224).

Based on previous research at the Cantonal Hospital of Aarau, there will be approximately 180 to 200 patients with UTI in a 12-month period, of which approximately 75 are expected to consent to this trial. Thus we estimate to complete the trial within 36 months.

The necessary sample sizes are shown in Table 2 assuming varying differences in LOS and antibiotic duration between the two intervention groups. Therefore, we will aim for a sample size of 250.

**Table 2 T2:** Sample size considerations

**Time 1**	**Time 2**	**Power**	**Alpha-level**	**SD**	**Number per group**
10	8	0.8	0.05	4	63
10	8	0.8	0.05	5	99
10	8	0.8	0.05	6	142
10	9	0.8	0.05	4	252
10	9	0.8	0.05	5	393
10	9	0.8	0.05	6	566
6	4.5	0.8	0.05	4	112
6	4.5	0.8	0.05	5	175
6	4.5	0.8	0.05	6	252
6	5	0.8	0.05	4	252
6	5	0.8	0.05	5	393
6	5	0.8	0.05	6	566

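### Enrolling 250 with the stated 20% loss leaves 100 per arm, below the 112 that Intervention B needs: power for B is about 75%, not 80%

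*Protocol article*

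**What the plan says.** The Abstract (Methods and design) sets the numbers: "We plan to screen 300 patients and enroll 250 for an anticipated estimated loss of follow-up of 20"%. The next sentence concludes: "This will provide adequate power for the two interventions".

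The Sample size section gives each requirement:

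- **Intervention A:** antibiotic therapy "2 days shorter in the PCT group (8 days, standard deviation ±5) than in the control group (10 days, standard deviation ±5"), which leads to 99 patients per arm for 80% power at the 5% level.
- **Intervention B:** control length of stay "which approximated 6 days (standard deviation ±4"), with the working hypothesis that "index hospitalization is 1.5 days shorter in the ProADM group (4.5 days, standard deviation ±4"). The result is that "112 patients per arm would provide an 80% power at the 5% alpha level (total sample size 224").

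After referring to Table 2, the section ends: "Therefore, we will aim for a sample size of 250". It shows no allowance for loss. The 20% appears only in the Abstract.

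**The concern.** The Abstract ties the enrolment figure to a 20% loss to follow-up and says that the result is adequate for both interventions. That holds only if 80% of 250 still meets the larger of the two requirements, which is B's 224. It does not.

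The step from 300 to 250 does not help. Since 250 x 1.2 = 300, the 20% seems to have been used as a margin between screening and enrolment. Loss to follow-up happens after enrolment, and screening more patients does not replace those lost later.

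At stake is how a null result for ProADM-guided triage would be read. A reader would take it as coming from a comparison with the conventional 80% power, which the stated design does not give.

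**Working it through.** **Inputs.** Enrolment 250 and loss 20% (Abstract); 1:1 allocation in each of two independent randomizations (Methods, opening paragraph); A: difference 2 days, SD 5; B: difference 1.5 days, SD 4; 80% power and 5% alpha (Sample size section). Sidedness is not stated. The two-sided formula reproduces the protocol's figures, while a one-sided one gives 88 per arm for B, so two-sided is used.

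**1. Reproduce the protocol's figures.** n per arm = 2 x [(1.960 + 0.842) x SD / difference]^2.

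- A: 2 x (2.8016 x 5 / 2)^2 = 98.1, rounded up to 99.
- B: 2 x (2.8016 x 4 / 1.5)^2 = 111.6, rounded up to 112.

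Both match, as do all 12 rows of Table 2.

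**2. Apply the stated loss.** 250 x (1 - 0.20) = 200 evaluable, or 100 per arm. That is at least 99 for A but below 112 for B.

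**3. Power at 100 per arm.** Power = Phi(difference / [SD x sqrt(2/n)] - 1.960), ignoring the negligible opposite tail.

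- A: 2 / (5 x sqrt(0.02)) = 2.828; Phi(0.868) = 80.7%.
- B: 1.5 / (4 x sqrt(0.02)) = 2.652; Phi(0.692) = 75.5%.

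The noncentral t calculation gives 80.4% for A and 75.1% for B.

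**4. Detectable difference for B at 80% power.** 2.8016 x 4 x sqrt(2/100) = 1.58 days (1.59 with the t distribution), against the planned 1.5.

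**5. Enrolment needed at 20% loss.**

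- A: 198 / 0.8 = 247.5, so 248.
- B: 224 / 0.8 = 280.

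The figure of 250 fits A and is 30 short for B. Even the looser inflation 224 x 1.2 = 268.8 (269) exceeds 250.

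**6. Loss that B can bear with 250 enrolled.** 1 - 224/250 = 10.4%.

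**7. Power for B as a function of loss** (normal approximation, 250 enrolled):

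| Loss of B's endpoint | Evaluable per arm | Power for B |
|---|---|---|
| 0% | 125 | 84.2% |
| 10.4% | 112 | 80.1% |
| 20% (as stated) | 100 | 75.5% |

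**8. Planned test.** The primary test is Mann-Whitney, whereas the sample size comes from a two-means formula. If the data were normal, an assumed relative efficiency of 0.955 would cut the 100 per arm to an effective 95.5. On the t calculation that gives about 73% for B and 78% to 79% for A. Lengths of stay are usually skewed, and the rank test may then do better or worse, so these figures are only indicative.

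**The case against.** The best counter-argument is that 20% is the wrong loss to apply to B. The protocol sizes B on index hospitalization, defines length of stay as days of physician-led hospitalization until discharge to ambulatory or nurse-led care, and follows patients by telephone at days 30 and 90. A patient who misses a call has not lost the index stay. The primary population is also the full analysis set under intention to treat, with the evaluable-only analysis as a sensitivity analysis. If all 250 contribute, B has 84% power.

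Much of this is fair, and it shows that 75% is B's power under the stated loss rather than an unconditional fact. It does not rescue the claim as written, for three reasons:

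- B's endpoint is defined over a follow-up window (30 days in the Abstract, 90 days under Outcomes and adverse events), so readmission days can be missed.
- Statistical considerations gives no way of supplying a missing primary outcome. Keeping a patient in the analysis set does not restore the information.
- The protocol gives one loss figure, 20%, ties it to the 250, and nowhere states a lower one for B.

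A second objection is that the 20% is really screening attrition, mislabelled. The 300/250 ratio makes this plausible. But the text says loss of follow-up, and if screening attrition was meant, the sentence is wrong and no loss after enrolment has been stated. It needs correcting on either reading.

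Third, the effect is small: about 5 points of power, or a detectable difference less than 0.1 day larger. Uncertainty in the SD matters more, since Table 2 shows that an SD of 5 raises B's requirement from 112 to 175 per arm. That stands as a comment on size, but the conflict between the stated figures remains.

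**Conclusion.** The concern holds. On the protocol's own enrolment, loss, effect sizes and SDs, 250 enrolled gives about 80% power for A and about 75% for B, so the statement that power is adequate for both is not supported. The shortfall is modest.

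The 75% rests on the two-sided two-means formula behind the protocol's sample sizes, on SD 4, and on the 20% loss applying to B's primary endpoint. If B's endpoint were complete, power would be 84%; the break-even loss is 10.4%. The documents do not say that B's loss is below that.

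**What to change.** Amend the Abstract and the Sample size section in one of two ways:

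1. **Keep the 20% loss.** State that 250 enrolled leaves 200 evaluable (100 per arm), with 80% power for A, 75% power for B, and a difference detectable with 80% power for B of about 1.6 days.
2. **Separate the losses.** If length of physician-led stay is taken from hospital records for every patient, say so, and state and justify a B-specific loss of at most 10%, which is what 80% power for B requires.

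In both cases, delete the unqualified claim of adequate power for the two interventions, and say whether the 20% refers to loss after enrolment or to the step from screening to enrolment.

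The cost is wording only; under the first option the stated power for B becomes slightly less favourable. Enrolling 280 would also close the gap, but at the protocol's expected 75 consenting patients a year that is 280/75 = 3.7 years, against the planned 36 months.

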**Discussion:**

This trial investigates two strategies for improved individualized medical care in patients with UTI. The minimally effective duration of antibiotic therapy is not known for UTIs, which is important for reducing the selection pressure for antibiotic resistance, costs and drug-related side effects. Triage decisions must be improved to reflect the true medical, biopsychosocial and functional risks in order to allocate patients to the most appropriate care setting and reduce hospital-acquired disability.

**Trial registration:**

Trial registration number:
ISRCTN13663741

## Background

Urinary tract infections (UTIs) include acute cystitis (involving the lower urinary tract) and acute pyelonephritis (involving the upper urinary tract). If a structural or functional abnormality is present, the UTI is considered ‘complicated’, implying a higher risk of encountering antimicrobial resistance and therapy failure [1]. *Escherichia coli* has been identified as the most common causative pathogen in uncomplicated (75%) as well as in complicated UTIs (40% to 50%) [2].

Current empiric antibiotic therapy schemes for UTIs are based on guidelines that largely reflect expert opinion [3,4]. There are few intervention studies comparing different durations of antibiotic therapy [5-7]. Considering the emerging antibiotic resistance of uropathogens [2,8,9] and the growing awareness of the epidemiological side effects of antibiotics [10], efforts aimed at improvements should be intensified.

There is increasing interest in biomarkers as diagnostic and prognostic factors in infectious diseases since they reflect the host’s response and are objective, dynamic and easily measurable. In particular, the biomarker procalcitonin (PCT) has been thoroughly investigated and has been proven to be a useful tool in managing the antibiotic therapy of bacterial infections of the respiratory tract [11,12]. In a previous multicenter study of patients with sepsis admitted to French intensive care units (ICUs), a PCT-guided strategy for treating bacterial infections safely reduced antibiotic exposure compared to present guidelines [13]. Of note, 7% of the enrolled patients had a UTI as their source of infection. PCT primarily indicates systemic infections. Thus, in patients with UTIs, PCT likely needs to be combined with inflammatory surrogates of local infection [14] such as pyuria or a urinary protein profile. The normalization of pyuria or a drop of at least 90% in urinary leukocytes correlated with a successful outcome of UTI therapy [15]. The tubular injury marker, the α1-microglobulin/creatinine ratio, has a high specificity and sensitivity in distinguishing pyelonephritis from cystitis and is positively correlated with baseline C-reactive protein (CRP) levels [16-18].

Radiologic evaluation of the urinary tract in patients with a febrile UTI is frequently performed. The European Association of Urology recommends ultrasound evaluation to rule out obstruction and renal stone disease. Additional radiologic testing (for example, computed tomography, excretory urogram or 99mTechnetium-dimercaptosuccinic acid scan) ‘should be considered’ if fever persists after 72 h of treatment [19]. A more selective approach to imaging using a clinical prediction rule has been advocated [20]. Contrast-enhanced ultrasound (CEUS) is a promising method for detecting acute pyelonephritis [21]. Its sensitivity and specificity might approach that of computed tomography [22], but the available data are very limited.

In adults ≥65 years, UTIs are the second most common cause for hospitalization among infectious diseases [23] with an annual cost of approximately $1.6 billion in the USA alone [24]. Older patients have a high risk of becoming functionally impaired or lose their self-care abilities if they are hospitalized [25], possibly leading to further inpatient treatment or an increased length of stay (LOS) whereas outpatient treatment is less expensive [26] and carries a lower risk of subsequent disability. Particularly for lower respiratory tract infections (LRTIs), many patients are hospitalized for fear of medical complications [27] or for medical co-morbidities, functional and psychosocial reasons, despite a low-risk classification according to clinical severity scores [26,28]. Accordingly, one-fifth of low-risk inpatients with community acquired pneumonia (CAP) do not have any contraindications for outpatient treatment or identifiable risk factors for hospitalization [28]. Multidisciplinary assessment in order to triage to the most appropriate care setting [29-31], as well as innovative pathway bundles are important in reducing the hospitalization rate, LOS, antibiotic use and overall costs while achieving similar quality of life and patient outcomes as explored for LRTI [32,33]. For UTIs equivalent studies are lacking so far, but as evident in daily clinical practice, improved triage for these infections is urgently needed. For LRTI we showed that ProADM was the most accurate biomarker for prognostic assessment [31,34,35]. As it is not specific for LRTIs, we propose that ProADM will be an excellent marker for prediction of re-hospitalization and death in UTIs [36].

## Methods

This is a randomized controlled open-label trial using a two-by-two factorial study design with two independent internet-based 1:1 randomizations (one each for the antibiotic part and one for the triage part, respectively) (Figure 1). The objectives are first, for Intervention A, to analyze the efficacy and safety of a PCT- and pyuria-guided antibiotic therapy in individualizing and reducing the duration of antibiotic treatment compared to the guidelines [4,10,19,37] and second, for Intervention B, to test the impact on LOS of ProADM-enhanced triage decisions compared to standard care. Both interventions are for a high-intensity implementation of interdisciplinary risk assessment for triage in patients with UTIs presenting to an ED. LOS is defined as the number of days of physician-led hospitalization until discharge to ambulatory or nurse-led care.

**Figure 1 F1:**
[figure not shown]
**Trial overview.** D1: day 1; D3: day 3; D5: day 5; D7: day 7; D30: day 30.

The trial is supervised by an independent safety monitoring board, which is not involved in the design and conduct of the trial. The board consists of three experts in internal medicine, infectious diseases, nephrology and epidemiology, respectively.

Ethical approval for this trial, which is in compliance with the Helsinki Declaration and in agreement with the CONSORT statement [38], has been obtained from the local ethical committee. The institutional review board of the Canton Aargau approved the study protocol. All participating patients or their relatives must give written informed consent.

### Setting

In April 2012, we started to screen all adult patients with a suspected UTI admitted to the ED of the public Cantonal Hospital of Aarau, a tertiary-care 600-bed hospital in northern Switzerland. We expect to finish the study by December 2014.

Physicians in charge of patient recruitment and inclusion and nursing staff attended a structured seminar on evidence-based guidelines for the management of patients with UTIs, the details of the protocol, the rationale and the design of the trial and the online website.

### Participants

Inclusion criteria for patients are age ≥18 years and admission from the community or a nursing home with a main diagnosis of acute UTI (that is, symptoms less than 28 days). Exclusion criteria are other infections that require an antibiotic therapy, pre-treatment with antibiotics within the last 48 h, pregnancy, prostatitis (defined as pain on digital rectal examination or a Prostate-speicifc antigen (PSA) > 4 ng/ml or PSA > 2× baseline) presence of implanted foreign bodies in the urinary tract or urinary catheters, endovascular prostheses or foreign bodies, non-endovascular prostheses or foreign bodies within 6 months after implantation, insufficient language skills with no possibility for translation, foreseeable non-compliance for follow-up (for example, current drug abuse), severe immunodeficiency (neutrophiles <500/μL, CD4 cells <350/μL in patients with HIV infection, leukemia, lymphoma, myeloma, cytotoxic medications, hemodialysis, transplant patients) or severe medical co-morbidity with imminent death.

### Definitions

UTI is defined by at least one clinical symptom (core body temperature ≥38.0°C, urinary urgency, polyuria, dysuria, suprapubic pain, flank pain, costovertebral angle tenderness, nausea and vomiting) and one urinary criterion (pyuria >20 leukocytes/μl [39] and/or nitrites). A UTI is defined as febrile UTI/pyelonephritis if there is flank pain, costovertebral angle tenderness or a body temperature ≥38°C, and otherwise as simple UTI. A UTI is defined as complicated if any of the following criteria are fulfilled: male gender, age >70 years, symptoms >7 days, recent antibiotic therapy (within 30 days), recurrent UTIs (two or more during the last 6 months or three during the last 12 months), recent urologic intervention (30 days), functional or anatomic abnormality, diabetes mellitus or immunosuppressive therapy; otherwise UTI is considered uncomplicated for example, young non-pregnant women.

### Randomization

Randomization of patients to either intervention is based on a pre-specified computer-generated randomization list and concealed by using a centralized password-secured website. Based on the factorial design, the two randomizations are independent.

### Interventions

With enrollment of each patient, the physician in charge is reminded of the processes of care in the ED. The recommendations include the choice of antibiotic therapy and duration as well as site-of-care decisions, together with reminders about biopsychosocial and functional overruling criteria and medical risk.

#### Intervention A

Appropriate antibiotics and minimal duration of antibiotic treatment are based on recent guidelines [10] after local adaptation by a panel of experts. PCT is used to guide antibiotic treatment (Figure 2). We use fosfomycin (3 g single dose) [40] and trimethoprim-sulfamethoxazole (800/160 mg twice daily) for simple UTIs. Furthermore we use ciprofloxacin orally (500 mg twice daily or 250 mg twice daily if the estimated glomerular filtration rate <30 ml/min/1.73 m2) or ceftriaxone intravenously (2 g daily) for febrile UTIs/pyelonephritis. If known, previous antibiotic resistant profiles are considered. If there is a non-susceptible urine pathogen in the current urine culture the antibiotic therapy is adjusted. In inpatients, antibiotic duration is based on absolute values of PCT and relative decreases of PCT levels and pyuria. In outpatients, the antibiotic duration is based on absolute values of PCT only. PCT and pyuria are measured on admission, and, in hospitalized patients, every other day as long as the patient receives antibiotics for the UTI. Pyuria criteria are derived from local data on female patients with UTIs [15]. PCT cutoffs are derived from data from our recent observational study and after extrapolation from patients with LRTIs and sepsis [36,41,42]. Patients with uncomplicated simple UTIs in the PCT group receive NSAIDs regardless of PCT values for symptom resolution given emerging data [43,44]. In the control group, antibiotic durations are recommended based on guidelines (Figure 2).

**Figure 2 F2:**
[figure not shown]
**Individualized antibiotic guidance by PCT and pyuria.** The algorithm for diagnostic purposes is shown. If there is any concern about microbiologic resistance, therapy extension is considered. For proven microbiologic resistance therapy is adjusted. Remaining antibiotic treatment after patient discharge is guided by last PCT value to result in total antibiotic duration in analogy to outpatient treatment. Abx: antibiotics; GFR: estimated glomerular filtration rate with MDRD formula; ICU: intensive care unit; NSAIDs: nonsteroidal anti-inflammatory drugs; PCT: procalcitonin; TMP-SMX: trimethoprim-sulfamethoxazole; UST: urinalysis; UTI: urinary tract infection.

Since failure of pyuria to decrease at least 90% within 24 h of antibiotic therapy was associated with treatment failure in patients with lower UTIs [15], we collect a urine specimen after 48 h (day 3) of antibiotic therapy in all patients. If patients are already at home at this time, they are given a container for urine to be returned for a urinalysis including determination of pyuria (Figure 1). We also collect urine for urinalysis and urine culture on day 7 after end of therapy, day 30 after enrollment, and in case of recurrence within 90 days. The patients are instructed to collect clean midstream urine into sterile urine containers. A vacuum is used to transfer the urine from the container to special urine tubes: BD Vacutainer® Plus Preservative Tube with ethyl paraben, sodium propionate and chlorhexidine preservatives for urinalysis and BD Vacutainer® Plus C&S Preservative Tube with boric acid, sodium formate and sodium borate for urine culture. These urine specimens are sent by priority mail in prestamped envelopes immediately after collection. Priority mail requires typically less than 24 h (maximum 48 h) to arrive at our hospital laboratory.

